**COVID-19 Sub-study**

The outcomes for patients with advanced CKD, patients with kidney transplants and patients on dialysis are amongst the worst of all patient groups (41). Not only are mortality rates significantly higher than in the general population, but patients with CKD are more likely to develop the most severe complications of COVID and are more susceptible to physical deconditioning from acute illness (42). The long-term effects of COVID-19 on physical activity, cardio-respiratory fitness and sarcopenia are also not known for patients with CKD. Additionally, acute kidney injury complicates up to 25% of patients admitted to intensive care units with COVID (43). It is anticipated that a proportion of patients that survive will have varying degrees of CKD and programs of post-COVID rehabilitation do not exist for either patients previously known to have CKD or patients recovering from the effects of COVID-induced AKI.

The Kidney Beam trial will contain an exploratory sub-study for any patients with CKD who had COVID-19 or who have been left with CKD following AKI-related to COVID-19 infection. At the baseline study (below) all patients will be asked about whether they have had a positive test for COVID-19. For those who had a positive test, an assessment of the severity of their COVID will be made in the following way:

- COVID positive, managed at home not requiring hospital admission
- COVID positive, required hospital admission but no oxygen therapy
- COVID positive, required hospital admission and oxygen therapy
- COVID positive, required hospital admission and non-invasive ventilation
- COVID positive, required hospital admission and admission to intensive care

Additional details of the admission, including length of stay and time since discharge will be recorded. Subjects will continue in the study in the same way but will complete the post-COVID functional status tool questionnaire at baseline and follow-up in addition to other outcome measures (44).

This exploratory sub-study will be a low-cost, high-yield way of gathering data to inform the design of more bespoke studies and interventions to meet the needs of post-COVID CKD patients and those recovering from the effects of post-COVID AKI.

**Polycystic Kidney Disease Sub-study**

Recommendations by ‘Kidney Disease: Improving Global Outcomes’ (KDIGO) for individuals affected by and at-risk of PKD include a healthy lifestyle and diet, maintenance of optimal weight, regular exercise, and avoidance of smoking. Nevertheless, despite these recommendations, little is known about the effectiveness of PKD-specific lifestyle modifications in improving quality of life, physical function and patient activation. The Kidney Beam platform, which is now widely available for people living with kidney disease in the UK, is an ideal place to create a bespoke education and exercise training module to support people living with PKD to engage with physical activity.

The Kidney Beam Trial will contain an exploratory sub-study for 12 patients with PKD. Those patients will be directed to complete a PKD-specific education module prior to starting the exercise training as per protocol. Participants will complete baseline and 12-week assessments as per protocol, and will be invited to feedback on the acceptability of the module via semi-structured interviews.

**Haemodialysis Sub-study**

A sub-study will be conducted to explore the impact of using kidney beam within an in-centre haemodialysis patient population. This sub-group of patients have a high physical health burden and this will help development of the platform to incorporate the needs of different users, with multi-morbidity and varied health needs who may normally find it more difficult to undertake physical exercise.

Evidence in intradialytic exercise programs is difficult to draw robust conclusions from as studies conducted in this area have yielded mixed results historically. An easily accessible exercise platform with the option for patients to utilise this whilst receiving their dialysis treatment could be beneficial.

A small group of haemodialysis patients (60) will be enrolled to this sub-study based on the inclusion and exclusion criteria listed in Section 4.3 with the additional inclusion criteria of:

- Receiving haemodialysis in-centre
- No instability on dialysis in the preceding 4 weeks prior to baseline visit
  - i.e. no episodes of intradialytic hypotension, early cessation of sessions for medical reasons or chest pain precipitated by dialysis

In line with the aforementioned goals of the Kidney Beam study, the following (taken from Section 7.3) will be measured pre and post 12 week kidney beam program with a view to ascertaining the benefit this population group receives:

- Physical functional parameters
  - Sit-to-Stand 60
  - Hand grip strength (in anticipation that some haemodialysis patients will have lower limb amputation or have lower limb disability)
- Quality of life measure (EQ5D-5L)

The patients will be separated equally in to three separate arms to evaluate the relevant benefits of supportive interventions in conjunction with kidney beam:

**Arm 1:** Access to Kidney Beam program

**Arm 2:** Access to Kidney Beam program plus equipment available for use on dialysis (exercise equipment plus IT equipment for access to kidney beam) – this will tie in with the other sub-study outlined in Section 7.8.

**Arm 3**: Access to kidney beam, available equipment on dialysis, regular visits from on-site staff – a mixture of both medical and physiotherapy staff – to provide practical tips on use of the platform, encouragement and motivation to continue with the program and supportive exercise options from the physiotherapy team.

This is with a view to building the knowledge base around exercise in dialysis patients to ascertain the level of intervention required to see beneficial changes.

Patient information sheets with be provided and informed consent will be taken face-to-face. Baseline data will be collected at initial visit as per methods in Section 7.3 but only measuring a selected number of parameters, as outlined above and then again at the 12 week visit as per Section 7.5, again measuring those select data parameters.

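### The haemodialysis sub-study cannot show the benefit of Kidney Beam from pre-post change, because all three arms receive Kidney Beam; it can compare support levels, if allocation is random

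*Protocol*

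**What the plan says.** The Haemodialysis Sub-study section opens with an exploratory intention: "A sub-study will be conducted to explore the impact of using kidney beam within an in-centre haemodialysis patient population". Its size is given as "A small group of haemodialysis patients (60) will be enrolled to this sub-study". The outcomes are the 60-second sit-to-stand test (STS60), hand grip strength and EQ5D-5L, taken before and after the 12-week programme "with a view to ascertaining the benefit this population group receives". The closing paragraphs of the section confirm that they are taken at baseline and week 12 only.

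On the arms it says: "The patients will be separated equally in to three separate arms to evaluate the relevant benefits of supportive interventions in conjunction with kidney beam". In the list that comes next, Arm 1 has access to Kidney Beam. Arm 2 adds exercise and IT equipment for use on dialysis. Arm 3 adds regular visits from on-site staff to that. A further aim follows the list of arms: "to ascertain the level of intervention required to see beneficial changes".

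No waitlist, usual-care or external comparison group is named for this sub-study. The main trial does have one: section 7.3.1 randomises participants to the platform or to a 12-week waitlist.

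**The concern.** The section sets two questions and builds a design for only one of them. What added support achieves on top of the platform can be studied by comparing the arms. What the platform itself does for in-centre haemodialysis patients needs patients without it, and there are none. The only route left to that question is change from baseline, and such change can occur with no treatment effect. Patients may do better on a second sit-to-stand or grip test because they know it. Entry also requires four weeks without instability on dialysis, so patients are selected at a favourable moment and may drift in either direction afterwards.

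The aim about the level of intervention required has the same weakness if it is read as finding the lowest arm in which scores improve, since that too rests on within-arm change.

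At stake is how an improvement would be interpreted. The protocol's Secondary Objectives section says that the trial's results are meant to support commissioning of the platform. An uncontrolled improvement described as benefit in haemodialysis could be given weight there that the design does not support.

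**Working it through.** **What each arm receives** (Haemodialysis Sub-study)

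| Arm | Kidney Beam | Equipment on dialysis | Staff visits | n |
|---|---|---|---|---|
| 1 | yes | no | no | 60/3 = 20 |
| 2 | yes | yes | no | 20 |
| 3 | yes | yes | yes | 20 |

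The available contrasts are Arm 2 v 1 (equipment), Arm 3 v 2 (staff visits) and Arm 3 v 1 (both). The Kidney Beam column is constant, so it cancels from every contrast. No patient is without the platform, and a larger sample would not alter that.

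**What pre-post change would show with no effect.** This illustration uses assumed drifts and correlations. Let r be the correlation between baseline and week 12, in units of the raw-score SD. The SD of change is √(2(1−r)). Suppose Kidney Beam does nothing and scores drift upward. A two-sided 5% one-sample test on all 60 patients is then significant with these probabilities:

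| Upward drift | r = 0.5 | r = 0.7 | r = 0.8 |
|---|---|---|---|
| 0.2 SD | 33% | 50% | 67% |
| 0.3 SD | 63% | 84% | 95% |

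The nominal rate is 5%. A downward drift would work the other way and hide a real benefit.

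**Precision of the contrasts the design supports.** The sub-study gives no effect size, SD, power or correlation for its 60 patients, so there is no figure of its own to reproduce. The only correlation in the protocol is 0.7, for the mental composite score (MCS) in section 10.1. That calculation does reproduce. The SD of change is 10 × √(2 × 0.3) = 7.75. A difference of 3 at two-sided 5% and 80% power needs 105.6 per group by the t-test, so 106 per group and 212 in total. With 30% dropout, 106/0.7 = 151.4, so 152 per group and 304 in total.

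For the sub-study, in units of the raw-score SD and for a single two-sided 5% comparison:

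- Unadjusted half-width of the 95% CI = t(0.975, 2n−2) × √(2/n). At n = 20: 2.024 × 0.316 = 0.64 SD.
- Unadjusted difference detectable at 80% power by the two-sample t-test, n = 20: 0.91 SD.
- Adjustment for baseline multiplies both by √(1−r²), ignoring the one degree of freedom spent. At r = 0.7 this is √0.51 = 0.714, giving 0.64 × 0.714 = 0.46 SD and 0.91 × 0.714 = 0.65 SD.
- An analysis of simple change scores at r = 0.7 would detect 0.91 × √0.6 = 0.70 SD.
- If the main trial's 30% dropout applied, n = 20 × 0.7 = 14 per arm. The unadjusted figures become 2.056 × 0.378 = 0.78 SD and 1.10 SD.

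**Allocation.** The haemodialysis text says "The patients will be separated equally in to three separate arms" and gives no method. The Ex-Tab Sub-study, in the same part of the protocol, says that its participants are randomised. Without random allocation, even the between-arm contrasts are open to confounding.

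**The case against.** The strongest reply is that one clause is being held against the stated scope. The section speaks of exploring, calls the group small, and says the work will help develop the platform. The arms exist "to evaluate the relevant benefits of supportive interventions in conjunction with kidney beam", and giving the platform to every arm suits that purpose. The sub-study plays no part in the primary analysis. All of this is true. It limits the weight of the point, but exploratory status lowers the certainty asked of a result and does not supply a missing comparator. The same holds for a statistical analysis plan: it could specify contrasts and adjustment, but it could not create patients without the platform.

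Main-trial waitlist patients on haemodialysis might serve as an outside reference for STS60 and EQ5D-5L. The protocol plans no such use, and the footnote to its procedures table limits grip strength to a subset at one site.

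Three stronger readings are tempting and are not supported:

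- A reader might infer that within-arm improvement will be reported as a Kidney Beam effect. The section names no within-arm test and section 10.3 sets out no analysis for this sub-study, so this is a risk and not a documented plan.
- A reader might infer that the sub-study is uninformative. It is not: three stepped levels of support bear on relative benefit by level, so the aim about the level required needs qualifying and not deleting.
- A reader might take 0.91 SD as the precision of any sensible analysis. It is the unadjusted figure, and baseline adjustment could improve on it appreciably.

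**Conclusion.** The point stands as one about the stated aim. The benefit of Kidney Beam in in-centre haemodialysis patients is not identified by this design at any sample size. That follows from the arm descriptions alone and needs no numerical assumption.

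The design can estimate the added benefit of support, provided that allocation is random. With 20 per arm those estimates will be imprecise: half-width 0.64 SD and detectable difference 0.91 SD unadjusted, or about 0.46 and 0.65 SD with baseline adjustment. The adjusted figures assume a correlation of 0.7, which the protocol gives only for MCS, an outcome that this sub-study does not list. The 14-per-arm figures assume that the main trial's dropout carries over, since the sub-study states none. The drift illustration rests wholly on assumed values and shows only that a significant pre-post change is weak evidence.

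The main trial's randomised waitlist comparison and its conclusion are unaffected.

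**What to change.** Amend the wording of the Haemodialysis Sub-study section in four places:

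1. Replace the aim of ascertaining benefit with two aims: to describe 12-week change in STS60, grip strength and EQ5D-5L, and to estimate, as exploratory, the baseline-adjusted between-arm differences (Arm 2 v 1, Arm 3 v 2, Arm 3 v 1) with 95% CIs.
2. State that allocation to the three arms is random.
3. State that within-arm pre-post change will not be interpreted as an effect of Kidney Beam.
4. Qualify the aim about the level of intervention required: it concerns relative benefit between support levels, and not the lowest arm that shows improvement.

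This needs no additional patients, arms or visits. If random allocation was not already intended, it also has to be put in place. The downside is a more modest claim for the sub-study. If the sponsor wants to keep the claim about Kidney Beam itself, wording will not be enough: a concurrent group without the platform would be needed.

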**Ex-Tab Sub-study**

The recruitment process for the Kidney Beam Trial excluded numerous participants due to not having Wi-Fi access, a suitable device to use and reports of participants not feeling confident to access an exercise platform online. This showed a significant number people living with CKD missing out on the opportunity to participate in the study. There is currently limited digital inclusion research of people living with CKD.

The Kidney Beam Trial will contain an exploratory sub-study of 40 participants from Kings College Hospital who do not have access to a digital device or who are not confident using the technology available to them. The participants will be randomised to receive the Kidney Beam platform intervention as per protocol or the exercise tablet intervention.

Participants will complete baseline and 12 week assessments as per protocol with the only difference being that a screening tool will be included to assess digital health literacy prior to inclusion and consent. All assessments for the participants in the exercise tablet intervention group will receive a face to face assessment, provision of a technology tablet, Wi-Fi access if needed, and training on how to use the device. The exercise tablet intervention group will be loaned a technology tablet for 12 (+- 2 weeks) so that they can access the Kidney Beam platform and engage in live or on demand classes.

Inclusion criteria:

Patients with established CKD

Aged 18 years+

Patients who are naïve to Kidney Beam intervention and who have not participated in a structured exercise programme in the prior 3 months

Patients that do not have an electronic device.

Patients that have self-reported low confidence using electronic devices.

Patients that do not have Wi-Fi access or data.

Exclusion criteria as per main study protocol.

### 5. Blinding

**5.1 Blinding**

Single-blind trial design whereby the Research Assistant who will conduct the outcome measures at baseline and 12 weeks will not be aware of the participant allocation.

### 6. Selection and Withdrawal of Subjects

### 6.1 Inclusion Criteria

- Individuals with established CKD
- Adults aged 18yrs+
- Access to a Wi-Fi-enabled device
- Able to understand written English language
- Written or virtual informed consent

### 6.2 Exclusion Criteria

- Weight < 50kg
- Self-reported participation in a structured exercise programme or kidney beam digital health intervention platform within previous 3 months
- Active infection
- Uncontrolled arrhythmias
- Unstable angina or heart attack within the 3 months
- Persistent uncontrolled hypertension (systolic blood pressure >180 mm Hg or diastolic blood pressure >110 mm Hg)
- Recent (within the last 3 months) stroke or transient ischaemic attack
- Receiving palliative care for advanced terminal cancer
- Patients with peripheral vascular or musculoskeletal disease, who the investigator deems unable to carry out a physical activity intervention.
- Any other health condition considered by the local Principal Investigator in which exercise therapy will be contraindicated.
- Insufficient understanding of the trial

**6.3 Selection of Participants**

Three hundred and four patients aged 18 years or over with established CKD will be enrolled. Each patient must meet all of the inclusion criteria, and none of the exclusion criteria, at entry to the trial. Patients who meet the entry criteria may be recruited by the investigator or any member of the local trial team who has delegated responsibility for trial recruitment.

The trial will be eligible for Clinical Research Network adoption. Replicating the study set-up and recruitment methodology employed in the Surveying People Experiencing young Adult Kidney failure (45), following Health Research Authority approval the trial will aim to run in all UK kidney units, allowing equitable access to the trial for all people with kidney disease in the UK. Local research nurses will identify and recruit patients and will be able to act as site Principal Investigators. Upon recruitment, the central trial research assistant

based at Kings College Hospital, will perform baseline assessments. Potential trial participants will be identified when presenting for their routine hospital clinic visits. Additionally, the local trial team may write to the patient, or phone them, to inform them of the study.

### 6.4 Randomisation Procedure

Randomisation (1:1) will be done on a secure web-based service. After passing the screening visit and when all eligibility criteria have been confirmed and informed consent has been received, the participants can be randomised into the study. Participants will be randomised using an approach based on randomly varying block sizes.

Randomisation will be done only by an unblinded member of staff who has been delegated this responsibility by the principal investigator as evidenced by documentation in the delegation log. The web-based database will allocate the participant a unique trial identification number and their identification details will be entered onto the trial identification log, which is kept in the Investigator Site File.

### 6.5 Withdrawal of Subjects

## Participants have the right to withdraw from the study at any time for any reason. The investigator also has the right to withdraw patients from the study treatment in the event of intercurrent illness, AEs, SAE’s, protocol violations, administrative reasons or other reasons. It is understood by all concerned that an excessive rate of withdrawals can render the study uninterpretable; therefore, unnecessary withdrawal of patients should be avoided. Withdrawn patients will not be replaced.

##

Withdrawal from study

## Should a patient decide to withdraw from the study, all efforts will be made to report the reason for withdrawal in as much detail as possible. Patients will continue to attend assessment visits and be followed up for adverse events.

Consent withdrawal

Participants have the right to withdraw their consent from further participation in the study at any time. Should a patient decide to withdraw consent, all efforts will be made to report the reason for withdrawal in as much detail as possible. After consent withdrawal, no further study data should be recorded or entered onto the database, although data queries arising from data recorded prior to the withdrawal of consent may be answered. The follow-up of participants who formally withdraw their consent will be censored at the date of withdrawal of consent.

### 7. Study Procedures

**7.1 Informed Consent**

Members of the local study team will screen for potential eligible study participants using the inclusion/exclusion criteria. The Principal Investigator leading the study team will confirm patient’s eligibility. Referrals from clinicians or clinical care team will also be screened for eligibility. After confirming potential eligibility, patients will be approached by an appropriately trained member of the study team to ascertain interest in entering the study. This individual will give a comprehensive verbal explanation of the trial (explaining both the intervention and the waitlist nature of the study and highlighting any possible benefits or risks relating to participation). Potential participants will be given adequate time throughout the discussion to ask any questions, and these will be suitably addressed. They will also be given a written information sheet about the trial and be given sufficient time (minimum 24 hours) to read and consider the study information prior to deciding whether to take part. If the participant is willing to take part, then they will be asked to sign the consent form. Remote recruitment and consent via telephone or video-conference will be utilised for those participants who are unable to attend a hospital visit.

No clinical trial procedures will be conducted prior to taking consent.

**7.2 Screening**

All data, as detailed below and in the Trial Flowchart, must be collected and all required procedures performed, to assess the subject eligibility for the study.

- Demographic assessments and baseline characteristics
  - Routine clinical information will be extracted from the medical notes and patient records including but not limited to: age, gender, ethnicity, cause of kidney disease, transplant type (if applicable), time since transplant (if applicable), dialysis-duration (if applicable), comorbidities, blood/urine results, medications, smoking habits, diabetes status, CV events and risk factors
- CRP, Creatinine, eGFR

A physical examination is not required in this study.

Patients who fail initial screening may be re-screened with there being no limit to the number of times a patient can be re-screened. Patients must agree to be rescreened and the discussion should be documented in the patient’s notes. Patients must be re-consented if the re-screening visit is more than 3 months from the initial patient consent.

Patients who pass a screening visit may be randomised to the study. Patients who fail a screening visit(s) may not be randomised to the study.

